### Data Analyses

#### Quantitative Data

Appropriate quantitative statistical analyses will be performed using SPSS (version 28; IBM Corp) in accordance with the type and distribution of data. The descriptive statistics are presented as median (IQR) values, means with SDs or 95% CIs, and frequencies of categorical data. The distributional properties of variables will be examined. Hypothesis testing will not be performed. In concordance with the Consolidated Standards of Reporting Trials (CONSORT) 2010 extension, estimates of effects using participant outcome measures (differences from baseline to postintervention) will be explored and reported as estimates with 95% CIs without *P* values [51,52]. We shall also perform mixed analyses; quantitative data can be supplemented from information in the qualitative material. For instance, if there is a change in the activity data, interviews can shed light on whether changes are related to the use of technology or whether other mechanisms are involved.

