**Methods:**

A mixed methods pilot study of an intervention arm will be carried out in a planned randomized controlled trial (RCT). Ten participants with ID and their caregivers or a staff member will be included. Information will always be provided by a caregiver or a staff member, or participants with ID if possible. Assessments will be carried out at baseline, follow-up after 4 weeks, and 12 weeks, and include questionnaires on PA, social support, self-efficacy, and challenging behavior. PA will be measured with 2 different activity trackers (Fitbit and Axivity) for 1 week at all assessments. Feasibility will be assessed as recruitment and adherence rate, missing data, usability of the motivational mHealth tool, and estimates of effectiveness. Acceptability of study procedures, activity measures, and motivation for participation in PA will be additionally assessed with qualitative methods at the end of the intervention.

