### Design

This protocol describes a mixed methods pilot study of an intervention arm in a planned RCT [27].

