### Participant Selection and Recruitment

Eligible participants will be identified through their participation in a larger study on health indicators for individuals with ID, the Norwegian Health in Intellectual Disability (NOHID) study, and through staff leaders at municipality levels who have identified potential participants [30]. Overall, 10 participants with ID as well as caregivers and support persons (ie, staff) will be included if they have a sedentary lifestyle or low levels of PA. A sedentary lifestyle is defined as primarily engaging in reading, watching TV, or other mainly sedentary activities. A low level of PA is defined as mainly walking or other light PA for less than 4 hours a week. The number of participants is chosen on the basis of assumptions about sufficient variation for the investigation of feasibility and acceptability of the pilot study [23]. Data saturation of qualitative data collected will be evaluated continually and there will be scope for flexibility to achieve this during the data collection period.

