#### Outcome Measures in the Definite RCT

To assess the planned primary outcome in the definite trial PA level (accelerometer measured steps per day) [26], the participants will use one Fitbit device (Versa). The watch will show a neutral screen during baseline and follow-up assessments. Participants who consent will, in addition, use one device manufactured for scientific purposes (Axivity AX3). Axivity will be used to assess the validity of the Fitbit Versa. This will objectively assess PA and sedentary time [38]. The PA level will be measured for 7 days at each assessment, with a minimum of 3 consecutive days of measurement [8]. Only days with at least 10 hours of wear time will be considered valid [39]. Many of the commercial fitness trackers have been validated for use in the research, including devices from Fitbit [40-42]. The primary outcome in the definite trial will be objectively measured PA assessed by increase in steps per day from the Fitbit device for each participant.

Several secondary outcome measures are explored: minutes of moderate activity, the International Physical Activity Questionnaire Short, BMI, and goal attainment [43-46]. Proxy respondent measures include measures of aberrant behavior (the Aberrant Behaviour Checklist-Community), social support for PA and self-efficacy in a PA setting, and health status (the EQ-5D scale) [47-49]. To control for adverse effects, an adapted quality-of-life scale will be assessed [50]. These measures will be used as evaluation of the sensitivity of the data to detect change and as part of testing the procedures for a later RCT. All these measures have previously been used in research with individuals with ID, and more information about each of these measures can be found in the protocol article for the planned RCT [27].

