## Discussion

### Expected Findings

In this pilot study, a possible main finding will be the large variations in the quality of the collected data. Many intervention studies including individuals with ID have recruitment problems [13], report that data are missing [12], and have a low participation rate, particularly for individuals with severe ID [5,6]. Conducting pilot trials is, therefore, important when planning RCTs since it offers the possibility to address feasibility issues, improve procedures, and prevent wastage of resources in future trials [52]. This knowledge can guide future development of technology-based PA programs and help improve future intervention studies aiming to improve levels of PA.

We expect that this pilot trial will uncover possible challenges in using technological devices for interventions aiming at PA promotion for individuals with ID. This pilot study will show how the use of a technological tool, such as mHealth, can be tested in research involving individuals with ID. The use of technology as a means of improving health has been explored to some extent in this population [20,21,55-57], but limited studies have investigated the use of mHealth for improving levels of PA for individuals with ID [25,58].

The quantitative measurements at baseline and follow-up may reveal differences in PA levels, self-efficacy of PA or in other psychosocial variables. In addition, we expect to find goal achievement among the participants by follow-up. We do not expect to detect any effects of the trial as it is a pilot study [59]. In addition, we expect a possible finding to be that the use of 2 activity trackers, Fitbit and Axivity, will strengthen the quality of activity data. We will gain experience in using one commercial and one research-friendly activity tracker. This experience can be useful in future trials.

In this pilot study, we expect that the use of the mHealth tool will rely on the caregivers or staffs’ involvement. The study will, therefore, offer insight into the inclusion of support persons in the planning of PA using mHealth tools, as previous research has shown a greater motivation for PA in individuals with ID if support persons are engaged and included in the activity [26]. It will also explore how the use of goal attainment for adults with ID can be used in a research project on PA promotion [60]. The influence of the use of technology on motivation for PA is being investigated through qualitative methods.

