### Conclusions

This pilot study will evaluate the feasibility and acceptability of study procedures of the intervention arm of a planned RCT. This can, in turn, address feasibility issues, improve study procedures, and estimate effectiveness of the study measures. We will investigate how technology can be used to influence motivation for PA, which can help guide and improve future PA interventions involving the use of technology. Investigating new ways of enhancing PA for individuals with ID is important to ensure better health and quality of life for this group.

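### With one arm and no comparator, the baseline-to-postintervention differences are within-participant change; they are not estimates of effect and cannot inform feasibility as estimates of effectiveness

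*Protocol article*

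**What the plan says.** The Design section states: "This protocol describes a mixed methods pilot study of an intervention arm in a planned RCT". The Abstract gives the size: "Ten participants with ID and their caregivers or a staff member will be included". Participant Selection and Recruitment gives its basis: "The number of participants is chosen on the basis of assumptions about sufficient variation for the investigation of feasibility and acceptability". No comparator is described for the pilot.

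On the analysis, the Quantitative Data section says that "estimates of effects using participant outcome measures (differences from baseline to postintervention) will be explored and reported as estimates with 95% CIs", without P values, and that no hypothesis tests will be done. It adds that interviews may help to show whether a change came from the technology or from something else.

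The purpose given to these differences varies by section:

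- **Abstract, Methods:** the list of feasibility measures ends with "usability of the motivational mHealth tool, and estimates of effectiveness".
- **Aspects of Feasibility:** the list is recruitment, adherence, retention and completeness of data. Effectiveness is not in it.
- **Outcome Measures in the Definite RCT:** "These measures will be used as evaluation of the sensitivity of the data to detect change", together with testing of procedures.
- **Expected Findings:** "We do not expect to detect any effects of the trial as it is a pilot study".
- **Conclusions (Abstract and main text):** the pilot will "improve study procedures, and estimate effectiveness of the study measures".

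Potential Limitations and Implications names the small sample, the possible refusal of two trackers, and participants who may already be interested in activity. It does not name the absence of a control group.

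**The concern.** An effect is a contrast between what happened with the intervention and what would have happened without it. One arm observes only the first. The difference from baseline would estimate the effect only if activity would otherwise have stayed the same, and nothing in the design secures that. Sources of change outside the intervention are visible in the article:

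- people enter because their activity is low;
- assessments are 12 weeks apart, in a study running from May 2021 to March 2022;
- trackers are worn repeatedly, and a study nurse makes contact at each follow-up.

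Study Context says that the results will be used to plan an RCT of 60 participants. If the change is reported under the name of an effect, a planner may carry it forward as the expected difference. A planner may also drop an outcome as insensitive because nothing moved, or keep one because something unrelated to the intervention moved it. Using observed change to judge sensitivity to change has the same weakness: without knowing whether true change occurred, a flat result does not separate an insensitive measure from an absence of change.

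**Working it through.** The plan has no figure to reproduce: the 10 participants rest on no alpha, power, effect size or SD. The calculations below show what the interval would and would not convey.

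**Inputs from the article:** n = 10; expected retention 80%, so 0.80 × 10 = 8; 95% CIs; paired differences; entry on a sedentary lifestyle or low activity. **Assumed:** correlation rho between baseline and follow-up of 0.5 to 0.9; entry from the lowest 30% or 50% of the activity distribution; a shift unrelated to the intervention of 0.3 or 0.5 SD of the change.

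**1. Sampling error of the mean change**, in SDs of the change: half-width = t(0.975, n−1)/√n.
- n = 10: 2.262/3.162 = 0.715
- n = 8: 2.365/2.828 = 0.836

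In between-person SDs, multiply by √(2(1−rho)), which is 1.00 at rho 0.5 and 0.447 at rho 0.9. This gives 0.72 to 0.32 for n = 10 and 0.84 to 0.37 for n = 8.

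**2. Precision of the SD itself**, as multiples of the estimate: √((n−1)/χ²).
- n = 10: 0.69 to 1.83
- n = 8: 0.66 to 2.04

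**3. Regression to the mean with no intervention effect.** For selection of the lowest fraction q on the same measure under bivariate normality, the expected rise in between-person SDs is (1−rho) × φ(c)/q, where c is the q quantile.
- q = 0.5: φ(c)/q = 0.399/0.5 = 0.798, so 0.40 at rho 0.5 and 0.08 at rho 0.9
- q = 0.3: φ(c)/q = 0.348/0.3 = 1.159, so 0.58 at rho 0.5 and 0.12 at rho 0.9

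The range is 0.08 to 0.58. It is an upper illustration, because entry is judged on described habitual activity and not on Fitbit steps, which weakens the mechanism.

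**4. How a shift unrelated to the intervention would appear in the CI.** From the noncentral t distribution with noncentrality d√n, the chance that the 95% CI lies wholly above zero is:

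| Shift d (SD of change) | n = 10 | n = 8 |
|---|---|---|
| 0 | 2.5% | 2.5% |
| 0.3 | 13% | 11% |
| 0.5 | 29% | 23% |

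Steps 3 and 4 show the direction and possible order of the problem; they do not predict its size here. As n grows, the half-width in step 1 shrinks while the shift stays the same.

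**The case against.** The strongest reply is that this is a matter of wording in an openly exploratory plan. The article rules out hypothesis tests and P values, and the phrase in question defines itself in brackets as a difference from baseline. It expects no effects to be detected and allows that change may have other causes. All of that stands, and it lowers the severity. It does not supply a comparator. Interviews can suggest explanations but cannot measure how much change would have happened anyway. The reporting guideline that the article cites may allow effect estimates in pilots, but it cannot identify an effect in a design without a control.

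Several stronger readings are tempting but not supported:

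- **Effectiveness as a feasibility criterion.** It appears in the Abstract's list only, has no threshold, and is absent from Aspects of Feasibility. What exists is a mismatch between the two lists.
- **A contradiction with the Discussion.** Reporting exploratory estimates and not expecting to detect effects can both be true.
- **The conclusions as a claim about the app.** The wording concerns effectiveness of the study measures, which may mean how the measures perform. It is ambiguous and needs rewording.
- **Goal setting and support-person involvement as confounders.** They are delivered with the intervention and are arguably part of it.
- **One common seasonal shift.** Participants were recruited individually over a period, so entry may have been spread over seasons. The article does not allow the direction or size to be stated.
- **Tracker reactivity as a large bias.** The watch shows a neutral screen during assessments, which should reduce it.
- **The pilot interval as wide as the RCT's whole target.** With 30 per arm (assumed 1:1, 80% power, two-sided 5%), the detectable difference is (1.96 + 0.84) × √(2/30) = 0.72 SD. That equals the pilot's half-width only if the SD of the change equals the SD of the outcome analysed in the RCT.

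**Conclusion.** The point holds as a should-fix. The baseline-to-postintervention differences are within-participant change. They are not estimates of effects and cannot provide the estimates of effectiveness that the Abstract lists under feasibility. This follows from the single-arm design and needs no assumption about numbers. The small sample adds imprecision: a half-width of 0.72 SD of the change at n = 10 and 0.84 at n = 8, none of which allows for bias. The size of that bias is unknown; the figures for regression to the mean and for an assumed shift are illustrations only.

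A reader might infer that the pilot's observed change will set the RCT's target difference or select its outcomes. The article does not say so: the RCT is already given as 60 participants, and its details are in a separate protocol. The risk is that the present labels leave that use open. The feasibility aims, the qualitative work and the descriptive analysis are unaffected.

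**What to change.** 1. **Quantitative Data:** replace the effect label with, for example, *within-participant change from baseline will be described with 95% CIs; it is not an estimate of intervention effect*.
2. **Abstract, Methods:** remove effectiveness from the feasibility list so that it no longer goes beyond Aspects of Feasibility.
3. **Conclusions, in the Abstract and the main text:** say instead that the pilot will describe how the measures perform, meaning completeness, variability and floor or ceiling.
4. **Potential Limitations and Implications:** add that there is no control group, so change cannot be attributed to the intervention.
5. **Use in the RCT:** state that the observed mean change will not be taken as the expected effect and will not be the sole ground for keeping or dropping an outcome. Where the SD is carried forward, give its CI, since 10 participants fix it only to 0.69 to 1.83 times the estimate.

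The article reports data collection as complete, and none of this needs new data or a larger sample. The cost is some rewording and the loss of an effectiveness claim that the design cannot support.

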#### Qualitative Data

The transcribed interviews will be analyzed in accordance with the principles of systematic text condensation [53]. This analysis follows a 4-step procedure. One author will perform the analysis and coding, while the other authors will contribute to further analysis, discussing interview content and preliminary findings, themes, and subthemes. The qualitative approach delivers data on feasibility of procedures, expectations, and the use of applications for PA, experiences with activity trackers and motivation for using technology to increase PA. In addition, clarity and discussion of minor themes and diverse cases will also be included to enhance trustworthiness and transferability to the findings. Reflexivity is a key issue to reflect on the conditions that might corrupt transferability and to adequately interpret the findings [53]. This reflection is imperative, particularly since the authors in this project strongly believe in the need for PA among individuals with ID as well as in the effect of the intervention approach. To facilitate such reflection, the coauthor validation procedure will be important. The consolidated criteria for reporting qualitative research will be utilized to ensure highest possible quality research in this pilot study [54].

## Results

Enrollment was initiated in May 2021 and was completed in March 2022. The participants were recruited and administered the intervention individually.

The main contribution of this protocol is a detailed description of a pilot trial that will produce knowledge on how to test procedures of future RCTs for PA among individuals with ID. In addition, this pilot trial will investigate how such individuals can be motivated to use mHealth tools. The trial is registered in ClinicalTrials.gov (NCT04929106).

## Discussion

### Expected Findings

In this pilot study, a possible main finding will be the large variations in the quality of the collected data. Many intervention studies including individuals with ID have recruitment problems [13], report that data are missing [12], and have a low participation rate, particularly for individuals with severe ID [5,6]. Conducting pilot trials is, therefore, important when planning RCTs since it offers the possibility to address feasibility issues, improve procedures, and prevent wastage of resources in future trials [52]. This knowledge can guide future development of technology-based PA programs and help improve future intervention studies aiming to improve levels of PA.

We expect that this pilot trial will uncover possible challenges in using technological devices for interventions aiming at PA promotion for individuals with ID. This pilot study will show how the use of a technological tool, such as mHealth, can be tested in research involving individuals with ID. The use of technology as a means of improving health has been explored to some extent in this population [20,21,55-57], but limited studies have investigated the use of mHealth for improving levels of PA for individuals with ID [25,58].

The quantitative measurements at baseline and follow-up may reveal differences in PA levels, self-efficacy of PA or in other psychosocial variables. In addition, we expect to find goal achievement among the participants by follow-up. We do not expect to detect any effects of the trial as it is a pilot study [59]. In addition, we expect a possible finding to be that the use of 2 activity trackers, Fitbit and Axivity, will strengthen the quality of activity data. We will gain experience in using one commercial and one research-friendly activity tracker. This experience can be useful in future trials.

In this pilot study, we expect that the use of the mHealth tool will rely on the caregivers or staffs’ involvement. The study will, therefore, offer insight into the inclusion of support persons in the planning of PA using mHealth tools, as previous research has shown a greater motivation for PA in individuals with ID if support persons are engaged and included in the activity [26]. It will also explore how the use of goal attainment for adults with ID can be used in a research project on PA promotion [60]. The influence of the use of technology on motivation for PA is being investigated through qualitative methods.

### Potential Limitations and Implications

This study will have several limitations. The sample size will be small, which will influence the representativeness of the quantitative data. For the qualitative data, a sample of 10 participants is expected to be of good quality if data saturation is achieved. Another limitation in the data collection can be that having 2 activity trackers might not be accepted by participants, resulting in no measurement if the participants stop using them. Participants or caretakers who agree to be included in the pilot study might be interested or engaged in PA promotion and the variation in the included participants regarding interest in PA might be scarce.

The study has potentially important implications for both individuals with ID and their support networks. The study will be presented at conferences and published in recognized international peer-reviewed journals.

### Conclusions

This pilot study will evaluate the feasibility and acceptability of study procedures of the intervention arm of a planned RCT. This can, in turn, address feasibility issues, improve study procedures, and estimate effectiveness of the study measures. We will investigate how technology can be used to influence motivation for PA, which can help guide and improve future PA interventions involving the use of technology. Investigating new ways of enhancing PA for individuals with ID is important to ensure better health and quality of life for this group.

## Appendix

Multimedia Appendix 1 Screenshots of the interface options of the Active Leisure app: symbols only, easy to read text, or plain text. The app also has read-aloud capabilities.

Multimedia Appendix 2 Screenshots of the augmented reality application “Sorterius”.

## Abbreviations

CONSORT: Consolidated Standards of Reporting Trials
ID: intellectual disability
mHealth: mobile health
NOHID: Norwegian Health in Intellectual Disability
PA: physical activity
RCT: randomized controlled trial
REDCap: Research Electronic Data Capture
